### Calculation of sample size

Sample size was firstly established by taking reference from a intervention study with the similar primary outcome (epigenetic age acceleration) [28]. In this study, 57 subjects were randomized to intervention and 58 subjects to the control groups, with a significant reversal of 0.66 years for epigenetic age acceleration. Nevertheless, given the secondary outcome frailty might require more sample size to achieve a significant improvement (the steps in Fried criteria are quite big), we referenced a multidomain study with 6-month interventions and 12-month follow up about frailty reversal [13].

In our study, each group will have 74 subjects to have 90% power to detect significant differences at *p* < 0.05 in epigenetic age acceleration and frailty changes at the 12-month follow-up based on a mixed linear model. Moreover, we considered the 20% dropout rate and 75% adherence [17], a total of 248 individuals will be recruited with 124 individuals in each group to ensure the efficacy of the study. Participants will be matched for chronological age, gender, smoking status, BMI for each group.

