### Randomization, blinding, and allocation concealment

Participants who meet the inclusion and exclusion criteria will be randomized into intervention and control groups in a 1:1 ratio. The randomization process will be carried out by a data custodian not involved in the study. The data custodian will generate a set of random numbers using a simple randomization procedure and place into sequentially numbered, sealed, opaque envelopes. The random numbers will be assigned to participants in numerical order. Participants in the intervention group will be informed about the intervention procedure and follow-up plan, while participants in the control group will be informed about the follow-up plan. If participants agree to their assigned plan, they will sign the informed consent and undergo further baseline assessment.

Due to the difficulty of blinding intervention implementers and participants in a multidomain intervention, data collection personnel and statistical analysts will be blinded to reduce bias. Participants are instructed not to disclose their group assignment to anyone during baseline and follow-up assessments.

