### Statistical analysis

This study will follow the intention-to-treat principle for statistical analysis, including participants who complete baseline assessments and at least one follow-up assessment in the final analysis. Normally distributed continuous variables with a normal distribution will be presented as mean ± standard deviation, while non-normally distributed continuous variables will be presented as median (interquartile range). Categorical variables will be presented as frequencies and percentages (%). For the baseline data comparison between the control group and the intervention group, independent samples t-test will be used for normally distributed continuous variables, Mann-Whitney U test for non-normally distributed continuous variables, and chi-square test or Fisher’s exact test for categorical variables. Repeated measures analysis of variance will be used to analyze the changes in primary and secondary outcomes within the intervention and control groups, with multiple comparisons corrected using Bonferroni adjustment. Repeated measures analysis of covariance will be employed to compare the differences in primary and secondary outcome measures between the intervention and control groups at different follow-up times. The statistical analysis will be conducted using R language version 4.0.3 and SPSS 25.0 statistical software. Hypothesis testing will be conducted using two-tailed tests with a significance level of α = 0.05, where *p* < 0.05 is considered statistically significant.

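### The sample size counts 25% non-adherence as lost participants although the analysis is intention-to-treat, so the stated 90% power is unsupported and could be as low as about 80%

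*Protocol article*

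**What the plan says.** Protocol article, Calculation of sample size: "each group will have 74 subjects to have 90% power to detect significant differences", at the 0.05 level, for epigenetic age acceleration and frailty at 12 months. Recruitment is then raised: "we considered the 20% dropout rate and 75% adherence [17], a total of 248 individuals will be recruited", that is, 124 per group. The adherence figure comes from a cited study, and the article does not say whether it is a share of participants or of sessions.

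Protocol article, Statistical analysis: "This study will follow the intention-to-treat principle for statistical analysis". The analysed set is everyone with a baseline and one or more later assessments. Adherence plays no part in that definition, and no adherer-only primary analysis is named. The test level is given as: "Hypothesis testing will be conducted using two-tailed tests with a significance level of α = 0.05".

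**The concern.** Dropout and non-adherence act differently under intention-to-treat. A dropout without outcome data lowers the number analysed, and dividing by 0.80 repairs that. A non-adherer who attends follow-up is still analysed, so the number stays the same and the mean difference shrinks. If non-adherers gain nothing, the difference shrinks by the factor 0.75. Because required sample size goes with the inverse square of the effect, the repair is then division by 0.75² and not by 0.75.

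The plan divides by 0.75 once, which suits an analysis restricted to adherers, and then specifies an analysis that keeps them all. At stake is the meaning of a null result. A reader who trusts 90% power would take the risk of missing the planned effect as 10%, when under the plan's own dropout and adherence inputs it could be about 20%.

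**Working it through.** **Inputs.** From Calculation of sample size: 74 per group, 90% power, 20% dropout, 75% adherence, 124 per group recruited. From Statistical analysis: two-sided α = 0.05, intention-to-treat. From the randomization section: 1:1 allocation.

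**1. Reproduce the plan's figure.** 74/(0.80 × 0.75) = 123.3, rounded up to 124; 2 × 124 = 248. This matches exactly. Other inflations do not:
- 74 × 1.2 × 1.25 = 111
- 74 × 1.2/0.75 = 118.4
- 74/(1 − 0.45) = 134.5
- 74/(0.80 × 0.75²) = 164.4

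So the adherence figure was applied once, as a loss of participants.

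**2. Standardized effect implied by 74 per group.** With the normal approximation for two means, d = (1.960 + 1.282) × √(2/74) = 0.533 SD. No raw SD is needed.

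**3. Number analysed.** 124 × 0.80 = 99.2, about 99 per group.

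**4. Power under intention-to-treat.** Let f be the fraction of the full benefit that non-adherers gain, and read 75% as the share of adherent participants among completers. The diluted effect is k × 0.533 with k = 0.75 + 0.25f, and power = Φ(k × 0.533 × √(99/2) − 1.960).

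| f | k | Power |
|---|---|---|
| 0 | 0.75 | 80.3% |
| 0.25 | 0.8125 | 86% |
| 0.5 | 0.875 | 91% |
| 0.75 | 0.9375 | 94% |
| 1 (no dilution) | 1 | 96% |

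For f = 0: 0.75 × 0.533 = 0.400; 0.400 × 7.036 = 2.81; 2.81 − 1.96 = 0.85; Φ(0.85) = 0.80. The noncentral t gives 80.4%.

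**5. Where 90% is met.** This needs k = √(74/99) = 0.865, so f = (0.865 − 0.75)/0.25 = 0.46. Non-adherers would have to keep about 46% of the benefit.

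**6. Size that would hold 90% at f = 0.** 74/0.75² = 131.6, so 132 analysed; 132/0.80 = 165 per group, 330 in total. This only shows the scale of the difference.

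**7. Sensitivity to the other inputs.**
- If all 124 per group were analysed and f = 0: Φ(0.400 × √(124/2) − 1.960) = 88%.
- If dropouts were mostly non-adherers, so that the 124 × 0.75 = 93 adherers are all among the 99 completers: k = 93/99 = 0.94, and power is about 94% even at f = 0.

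**The case against.** The strongest reply is that 80% is only one point in a range. Nothing in the article says that non-adherers gain nothing. At half the benefit power is 91%, and at about 46% it is exactly the stated 90%. The adherence figure is undefined. If it is a share of sessions, a proportional loss of effect is a further assumption. Dropout and non-adherence may overlap, which would leave fewer non-adherers among completers. Someone lost after month 6 may still contribute through the mixed linear model named in the sample size section, so 99 is not certain. All of this stands, and it is why the result is given as a range.

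Three stronger readings are tempting and are not supported:
- A reader might infer that power simply is 80% and not 90%. That holds only with zero benefit in non-adherers, 75% adherent among completers, and about 99 analysed per group. The article fixes none of these three.
- A reader might infer that 90% cannot hold on any reading. It can, at about 46% retained benefit, but the plan makes no such assumption.
- A reader might derive an SD from the cited 0.66 years and judge the 74 against it. The section says that frailty might need more participants and turns to a second study, so the 74 may have been set by frailty. The absence of an SD is detail that an article may leave to the full protocol.

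None of this rescues the method. The adherence adjustment still follows a rule that does not fit the stated analysis.

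**Conclusion.** The point holds in conditional form. The step from 74 to 124 treats non-adherers as absent, the analysis section keeps them, and the two sections do not fit together. For the comparison that the 74 was sized for, at two-sided 0.05, power is about 80% at zero benefit in non-adherers, 86% at a quarter and 91% at half. If the planning effect already included non-adherence, dividing by 0.75 was not needed and power is about 96%. The plan therefore does not show that 248 participants give 90%, and the type II error could be up to about twice the 10% implied.

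The figures rest on the back-calculated 0.533 SD, about 99 analysed per group, and 75% read as the share of adherent participants among completers. They cover one comparison without any multiplicity correction. Confidence is high that the inflation does not match the analysis, and medium for any single power value.

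**What to change.** Keep the total at 248 and rewrite the second paragraph of Calculation of sample size so that it:
- defines 75% adherence (participants or sessions, and whether among completers);
- applies it as dilution of the intention-to-treat effect and not as loss of participants;
- states about 99 analysed per group after 20% dropout;
- states the benefit assumed in non-adherers;
- replaces the 90% claim with the power that follows, about 80% at zero benefit, with a range of about 80% to 91% up to half benefit.

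If the planning effect is already an intention-to-treat effect, the section should say so and drop the adherence inflation from the argument.

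The cost is a less favourable stated figure. No participants are added, and the design and analysis do not change.

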### Epigenetic age acceleration and pace of aging

Our study will employ eight representative epigenetic aging clocks to estimate epigenetic age acceleration and pace of aging: Horvath [38], Hannum [39], PhenoAge [40], GrimAge [41], DunedinPACE [42], GrimAge version 2 [43], PC-PhenoAge and PC-GrimAge [44].

The first-generation epigenetic clocks, the Horvath clock and the Hannum clock, are constructed solely based on DNA methylation data. Horvath [38] developed an epigenetic clock comprising 353 CpG sites by analyzing publicly available DNA methylation datasets from a wide range of human tissues and cell types. Hannum et al. [39] created an epigenetic clock based on 71 CpG sites, utilizing DNA methylation data from the blood of adults. Both the Horvath and Hannum clocks exhibit high accuracy in predicting chronological age.

The second-generation epigenetic clocks, such as GrimAge and PhenoAge, incorporate clinical biomarkers in addition to methylation data. The PhenoAge clock integrates 9 clinical blood biomarkers (albumin, alkaline phosphatase, creatinine, C-reactive protein, glucose, mean corpuscular volume, red cell distribution width, white blood cell count, and lymphocyte percentage) and 513 age-related CpGs [40]. The GrimAge clock [41] is composed of 7 DNA methylation-based plasma protein biomarkers, pack-years of smoking, and 1030 CpG sites. The plasma protein biomarkers include cystatin C, leptin, tissue inhibitor of metalloproteinase 1 (TIMP-1), adrenomedullin (ADM), beta-2-microglobulin (β2-M), growth differentiation factor 15 (GDF-15), and plasminogen activation inhibitor 1 (PAI-1) [41]. Both GrimAge and PhenoAge demonstrate strong correlations with lifestyle risk factors and perform well in predicting morbidity and mortality risks.

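### The protocol says the groups will be matched on age, sex, smoking and BMI, but its simple randomisation balances these only in expectation, so the two statements cannot both be followed

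*Protocol article*

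**What the plan says.** The closing sentence of Calculation of sample size gives matching as a feature of the design: "Participants will be matched for chronological age, gender, smoking status, BMI for each group".

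Randomization, blinding, and allocation concealment describes how people reach an arm. They are "randomized into intervention and control groups in a 1:1 ratio". The mechanism is: "The data custodian will generate a set of random numbers using a simple randomization procedure and place into sequentially numbered, sealed, opaque envelopes". Then: "The random numbers will be assigned to participants in numerical order". Nothing in that section uses a participant's characteristics.

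The order of events also matters, because this is a Zelen design. Allocation comes first, and then: "If participants agree to their assigned plan, they will sign the informed consent and undergo further baseline assessment".

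Statistical analysis compares the arms at baseline with tests for independent groups, and compares outcomes between arms by repeated measures analysis of covariance. Neither uses matched pairs or sets.

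**The concern.** Matching means that a person's arm, or a person's inclusion, depends on the four factors. Handing out the next sealed number means that it does not. Site staff cannot do both, and a reader of the final report could not tell which was done.

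Two things are at stake. First, the protocol leads readers to expect balance on four named factors, and the stated procedure does not secure it. Smoking is the factor readers will look at first: the article says that the GrimAge clock "is composed of 7 DNA methylation-based plasma protein biomarkers, pack-years of smoking, and 1030 CpG sites", and GrimAge version 2 and PC-GrimAge are described as built on it, which makes three of the eight primary clocks. Second, the protocol leaves open how anyone would try to honour the matching sentence. Consent and baseline assessment follow allocation, so the text should rule out any balancing at that stage.

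**Working it through.** **Inputs from the protocol article.** 74 per arm for 90% power, 20% dropout, 75% adherence, 124 per arm and 248 in total (Calculation of sample size); 1:1 simple randomisation in numerical order (Randomization, blinding, and allocation concealment).

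**Inputs assumed.** The four factors are independent of each other. The SD of age is 6 to 7 years. Smoking prevalence is 10% to 30%. The protocol gives none of these.

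**1. The plan's own figure.** 74 / (0.80 × 0.75) = 123.3, rounded up to 124 per arm, or 248 in total. This reproduces, and nothing below changes it.

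**2. Balance on one factor.** With 124 per arm, the standardised difference between arms has standard error √(2/124) = 0.127.
- P(difference > 0.1 SD) = 2 × [1 − Φ(0.1/0.127)] = 43%
- P(difference > 0.2 SD) = 2 × [1 − Φ(0.2/0.127)] = 11.5%

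**3. Balance on four factors.** P(at least one beyond the limit) = 1 − (1 − p)⁴.
- Beyond 0.1 SD: about 90%
- Beyond 0.2 SD: 1 − (1 − 0.115)⁴ = 39%
- Beyond 0.25 SD: 18%

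A simulation of 20,000 trials with age and BMI continuous, sex at 50% and smoking at 10%, 20% or 30% gave 89–90%, 38–40% and 18–19%. If only 74 per arm were analysed, the 0.2 SD figure would be about 64%.

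**4. In natural units (95% chance limits at 124 per arm).**
- Mean age: 1.96 × 6 × √(2/124) = 1.5 years; with SD 7, 1.7 years
- Smoking at 15%: 1.96 × √(0.15 × 0.85 × 2/124) = 8.9 percentage points; across 10% to 30%, about 7.5 to 11.4 points

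**5. Arm sizes, if each number is an independent draw.** Binomial(248, 0.5) has SD √(248 × 0.25) = 7.87. P(exactly 124/124) = 5.1%, and the 95% range for one arm is 109 to 139. Efficiency relative to equal arms at that extreme is 4 × 109 × 139 / 248² = 98.5%.

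**The case against.** The strongest reply is that simple randomisation is a valid method. It balances all factors in expectation, chance imbalance does not bias the comparison, and the standard error allows for it. That stands. Choosing restricted randomisation at this sample size is a preference; what needs correcting is the claim of matching.

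Several stronger readings are tempting, and the document does not support them.

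- **That participants will be matched after allocation, causing selection bias.** A reader might infer this from the Zelen sequence. No sentence says that anyone is chosen, moved or dropped to make the arms alike, and sealed, opaque, sequentially numbered envelopes from an uninvolved custodian point the other way. It is a possibility worth excluding in words.
- **That equal arms will not be reached.** The 5% figure assumes independent draws. A shuffled list of 248 numbers would also fit the description and would give 124/124 exactly. Even without it, the efficiency loss is at most about 1.5% within the 95% range.
- **That imbalance carries straight into the primary outcome.** Seven of the eight clocks enter as residuals from a regression on chronological age, which largely removes age. The outcome is also a change, so a stable smoking difference largely cancels. No bias in the primary result has been shown.
- **That precision is lost, or that the unnamed covariates are a fault.** No loss has been quantified, and the covariates may be named in an analysis plan that is not shown.

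One could also read the matching sentence loosely, as meaning only that the arms should be comparable. Then it adds nothing to randomisation and still claims more than the method gives.

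**Conclusion.** The contradiction holds. It lies between two positive statements in the current text, so it is not a detail that a condensed article has left out. The allocation described is unbiased but does not match, and the document gives no mechanism by which it could.

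The size is moderate: about a 39% chance that at least one of the four named factors differs by more than 0.2 SD at 124 per arm. That figure rests on independence of the factors and on 0.2 SD as the yardstick; at 0.1 SD it is about 90%, at 0.25 SD about 18%. Unequal arm sizes are a side issue. The sample size is unaffected. The text should be corrected because it is cheap to do and because the report will otherwise claim a design feature that the trial did not have.

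**What to change.** **If enrolment has not started.** Have the same custodian prepare a permuted-block list with varying block sizes, stratified by sex and age band, both of which are known at screening. Replace the matching sentence with that description, and do not claim balance on smoking or BMI by design. Minimisation on all four factors is less suitable: it cannot run from pre-filled envelopes, and it needs smoking status before allocation, which Table 1 does not list at screening.

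**If enrolment has started.** Keep the allocation as it is and delete the matching sentence.

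**In either case.**
- Include age, sex, smoking status and BMI as covariates in the planned between-group analysis of covariance.
- State that nobody is selected, moved or dropped after allocation to achieve balance.

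**Cost.** One set of envelopes per stratum, and a few degrees of freedom in the model. Stratification balances those allocated; because consent comes later, refusals may still disturb the balance among those who enter, which is a further reason for the covariate adjustment.

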### Randomization, blinding, and allocation concealment

Participants who meet the inclusion and exclusion criteria will be randomized into intervention and control groups in a 1:1 ratio. The randomization process will be carried out by a data custodian not involved in the study. The data custodian will generate a set of random numbers using a simple randomization procedure and place into sequentially numbered, sealed, opaque envelopes. The random numbers will be assigned to participants in numerical order. Participants in the intervention group will be informed about the intervention procedure and follow-up plan, while participants in the control group will be informed about the follow-up plan. If participants agree to their assigned plan, they will sign the informed consent and undergo further baseline assessment.

Due to the difficulty of blinding intervention implementers and participants in a multidomain intervention, data collection personnel and statistical analysts will be blinded to reduce bias. Participants are instructed not to disclose their group assignment to anyone during baseline and follow-up assessments.

### Control group

Participants in the control group will attend a monthly health education lecture series conducted by the Fujian Provincial Center for Geriatrics, totaling 6 sessions. The content will include scientific exercise knowledge, dementia prevention, principles of a healthy diet, management of cardiovascular risk factors, and prevention of frailty and sarcopenia in older adults.

### Intervention group

Participants in the intervention group will receive a multidomain intervention including cognitive training, exercise training, and nutritional guidance for a duration of 6 months. The form of the multidomain intervention involves a combination of group and individual interventions. The group intervention sessions will be scheduled biweekly for a total of 12 sessions. Each session will last for 120 min, consisting of 60 min cognitive training, 45 min exercise training, and 15 min nutritional guidance.

After each group intervention session, participants will receive a physical booklet containing the content of the day’s cognitive, exercise, and nutritional intervention, and assignments for the individual family intervention (Supplementary materials). The goals of the individual family intervention include engaging in exercise training, cognitive training, and maintaining a record of healthy eating habits three times a week. Participants will log using the ‘SilverHealth Pro Platform’ app through mobile check-in records (Figure 1).

**Figure 1. F0001:**
[figure not shown]
Example of mobile check-in records through the ‘SilverHealth Pro Platform’ app in the individual family intervention. a: The main interface of the app allows participants to begin documenting their exercise training, cognitive training, and dietary records by clicking on ‘MIDA Health Diary’ Participants can view exercise examples in the form of pictures or videos by selecting different exercise options. b: In the exercise training section, participants will log the number of completed groups for each exercise movement. c: In the cognitive training section, participants will record the number of pages completed or the duration spent on each cognitive task from the cognitive training workbook. If needed, they can also upload pictures of the completed tasks. d: In the dietary record section, participants will sequentially log their daily meals, including staple foods, protein-rich foods, vegetables, fruits, and fats. If needed, they can upload pictures of their meals and add notes about the number of diners. This figure originates from software owned by the Fujian Provincial Center for Geriatrics and Fujian Provincial Institute of Clinical Geriatrics.

